## Abstract

**Background:**

Workplace mild traumatic brain injuries are frequently associated with persistent symptoms, leading to a reduction in productivity at work or even disability. People who sustain workplace injuries frequently need rehabilitation and support, and the challenges of delivering these services was heightened during the COVID-19 pandemic as injured workers had to be cared for remotely. Currently, clinicians are conducting both in-person and virtual (remote) concussion assessments; however, the measures that are being used to complete these assessments have undocumented psychometric properties.

**Objective:**

This study will document the psychometric properties of the clinical measures that are being used remotely and their ability to produce similar results to in-person assessments. Specifically, through this method-comparison study, we aim to (1) evaluate the sensitivity of the measures included in a virtual assessment toolkit when compared to an in-person assessment and (2) determine the interrater and intrarater reliabilities of the measures included in a virtual assessment toolkit.

**Methods:**

Patient participants (people living with acquired brain injuries) will attend two assessments (in person and virtual) at the Ottawa Hospital. The two assessments will be identical, consisting of the measures included in our previously developed virtual concussion assessment toolkit, which includes finger-to-nose testing, the Vestibular/Ocular Motor Screening tool, balance testing, cervical spine range of motion, saccades testing, and evaluation of effort. All virtual assessments will occur using the Microsoft Teams platform and will be audio/video-recorded. The clinician assessor and patient participant will complete a feedback form following completion of the assessments. A different clinician will also document the findings on observed videos of the virtual assessment shortly after completion of both in-person and virtual assessments and approximately 1 month later. Interrater reliability will be assessed by comparing the second clinician’s observation with the first clinician’s initial virtual assessment. Intrarater reliability will be evaluated by comparing the second clinician’s observation with their own assessment approximately 1 month later. Sensitivity will be documented by comparing the findings (identification of abnormality) of the in-person assessment completed by the initial clinician assessor with those of the second clinician assessor on the observation of the recording of the virtual assessment.

**Results:**

As of May 2024, we have recruited 7 clinician assessors and completed study assessments with 39 patient participants. The study recruitment is expected to be completed by September 2024.

**Conclusions:**

Currently, it is unknown if completing concussion assessments virtually produces similar results to the in-person assessment. This work will serve as a first step to determining the similarity of the virtual assessment to the matching in-person assessment and will provide information on the reliability of the virtual assessment.

**International Registered Report Identifier (IRRID):**

DERR1-10.2196/57663

## Introduction

### Background

A direct or indirect head impact leading to a concussion is a form of mild traumatic brain injury [1], which results in an alteration of brain functioning [2,3]. Most individuals who sustain a concussion experience rapid recovery within the first 2 weeks to 1 month following the injury. There are, however, instances where individuals continue to experience persistent symptoms after a concussion, with a reported occurrence of approximately 15%-20% [4]. These symptoms may persist beyond 1 year following the injury [3,5]. Factors such as premorbid characteristics (age, sex, concussion history), psychological factors, and injury-related factors (ie, severity of injury) are likely contributors to the persistence of the symptoms [6]. Postconcussion symptom presentation can vary widely, including cognitive deficits such as memory issues, vestibular deficits such as balance issues or dizziness, and ocular deficits such as blurred vision, among others [1,7-9]. There is a need for a multifactorial assessment approach due to the diversity in symptom presentation. Specifically, it is recommended to incorporate measures targeting each of the commonly experienced symptoms into a battery of tests [10].

There is evidence suggesting a growing documented incidence of concussion in the workplace context [11]. Kristman et al [12] reported that there are approximately 39-58 workplace concussions per 10,000 claims annually in Ontario, Canada [12]. Workplace concussions often lead to greater delays in return to work compared to injuries sustained outside of the workplace context [5,13]. It is estimated that roughly 60% to 90% of adults return to work within 6 months postconcussion injury, with the remainder continuing to be off work at this time point [5]. Compensation associated with a workplace injury may be a contributor to this delay in return to work [5,13].

Several factors can contribute to delays in return to work following concussion, including a lower level of education, more severe immediate symptoms post injury, and other injuries sustained [5]. In general, workplace concussions pose significant challenges. These include financial burdens that are felt by the health care system, employers, the Workplace Safety and Insurance Board (WSIB), and the workers themselves [14]. For the patient, lives are disrupted due to prolonged recovery times [13], resulting in the need for additional support from the WSIB for individuals presenting for specialized assessments.

The onset of the COVID-19 pandemic affected how specialized postconcussion assessments could be completed along with a need to switch to virtual care [15]. However, it is not known whether the measures being used by clinicians in virtual assessments are the same as those used for in-person assessments [16]. Additionally, the reliability of the virtual concussion assessments being conducted is unknown. Measures used in person that have shown strong psychometric properties may not produce the same or similar results when administered virtually [17]. Furthermore, the level of agreement between measures used in the in-person concussion assessment and those used in the virtual assessment has not yet been established. Currently, clinicians are continuing to complete both in-person and virtual concussion assessments; however, there is limited information on the measures used in the virtual assessment. It is important to gain an understanding of the properties of the clinical measures and their ability to produce similar results to the in-person assessment to inform the effectiveness of use in a virtual context [18].

The preparatory work for this study was initiated by developing a virtual assessment toolkit. Clinician surveys were used to identify relevant measures for assessing the physical domains of concussion [19]. A working group refined the measures feasible for virtual administration based on expert opinion. Focus groups then identified barriers and facilitators for virtual concussion assessments. The resulting virtual assessment toolkit was then used in a feasibility study to evaluate recruitment rates, procedure acceptability, and time to assess; the manuscript reporting these findings is currently being prepared for submission.

### Objectives

The objectives of this method-comparison study are two-fold: (1) to evaluate the sensitivity of the virtual assessment against the gold standard of the in-person assessment and (2) to determine interrater and intrarater reliabilities of the measures in the virtual assessment. This study will further contribute to the development of a virtual toolkit of assessments across four physical domains along with the evaluation of effort, specifically designed for the WSIB context.

## Methods

### Design

This study will follow a prospective method-comparison study design [17].

### Participants

#### Patient Participants

Eligible participants will be adults 18 years or older who have sustained an acquired brain injury (concussion or other form) and are being assessed by a physician, physician assistant, and/or physiotherapist at the Ottawa Hospital. In addition to people with concussions, people living with acquired brain injuries, including moderate to severe traumatic brain injury or hypoxic brain injury, will be recruited. In this study, we are assessing the consistency of physical examination findings; people with other forms of acquired brain injury such as severe traumatic brain injury more frequently have signs of central nervous system deficits, whereas these assessments are often normal during a postconcussion examination [20,21]. This inclusion is thus intended to ensure recruitment of participants with a broad range of identifiable deficits on all components of the assessment. Those unable to complete the study assessments and unable to speak English or French will be excluded from the study. Participant information will be documented, including demographics, functional status, environmental aids used, socioeconomic and work status, injury information, and information related to technology experience.

#### Clinician Participants

Clinicians with expertise in conducting assessments for people with acquired brain injuries will be invited to participate in this project. Demographic information for participating clinicians will be documented, including age, years practicing with patients who have an acquired brain injury, professional background (physiotherapist, physician assistant, physiatrist, other), and self-reports of competency with in-person and virtual neurological assessments.

### Sample Size

The target sample size of this method-comparison study is 60 patient participants. For the objective of assessing the sensitivity of the virtual assessment against the gold standard of in-person assessment, with a total of 60 participants, 50 (83%) of whom are expected to have an abnormal finding, and an estimated sensitivity ranging from 77% to 96%, the two-sided 95% CI around the estimated sensitivity will have a total width ranging from 8.7% to 25.3% (or margin of error 4.4%-12.7%). For the objective of assessing interrater agreement between two clinicians conducting a virtual assessment using the κ statistic, a sample size of 60 participants achieves 80% power to detect a true κ value of 0.89 using a one-sided test at the 5% significance level, assuming that 90% of participants are classified as abnormal; κ under the null hypothesis was specified as 0.5.

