#### Method-Comparison (Sensitivity) Analysis

The sensitivity of the virtual assessment compared to the gold-standard in-person assessment (rater A in person vs rater A virtual) will be determined, where the assessment of the uncertain classification of the measures used virtually will occur against the gold standard or “true” classification, which is the in-person assessment in this study. The findings of the initial clinician assessor (rater A) that completed the in-person and virtual assessments will be compared to determine the sensitivity of the measures administered virtually. In this case, sensitivity (true positives divided by the sum of true positives and false negatives multiplied by 100) refers to the ability of the virtual measure to identify a deficit or positive finding when the in-person measure identifies the deficit or positive finding. Values closer to 100% indicate greater sensitivity.

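### The planned CI widths for sensitivity hold only for a measure with about 50 in-person abnormal participants, which the plan neither states nor secures; the 8.7% end also does not follow from 96%

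*Protocol article*

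**What the plan says.** The Sample Size section sets the total: "The target sample size of this method-comparison study is 60 patient participants". For the sensitivity objective it continues: "with a total of 60 participants, 50 (83%) of whom are expected to have an abnormal finding". It assumes "an estimated sensitivity ranging from 77% to 96" per cent and concludes that "the two-sided 95% CI around the estimated sensitivity will have a total width ranging from 8.7% to 25.3" per cent, also given as a "margin of error 4.4%-12.7" per cent. One abnormal count and one range of widths serve the whole objective.

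The objective and the analysis are about individual measures. The Abstract (Objective) aims to "evaluate the sensitivity of the measures included in a virtual assessment toolkit when compared to an in-person assessment". The Outcomes section lists a binary abnormality classification for six items: finger-to-nose, VOMS, balance, cervical range of motion, saccades and effort. Under Method-Comparison (Sensitivity) Analysis, rater A's two sets of findings "will be compared to determine the sensitivity of the measures administered virtually", and a positive on the virtual measure is judged against a positive on the same measure in person.

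On how often abnormality occurs, the Patient Participants section under Participants says that "these assessments are often normal during a postconcussion examination". It gives this as the reason for also enrolling people with more severe or hypoxic brain injury. Recruitment and Consent adds purposive sampling across all domains. Neither section gives an expected or minimum number of abnormal participants for any measure.

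**The concern.** The precision of a sensitivity estimate depends on its own denominator, here the participants abnormal in person on that measure. The plan supplies a single number, 50, described as participants with an abnormal finding, and does not say whether this means at least one abnormality anywhere or an assumed rate for every measure. On the first reading the stated widths do not describe the per-measure analysis. On the second, 83% abnormal is assumed for six different tests without support. Effort is the most doubtful case: it is recorded as full use of effort, yes or no (Table 1), so 50 abnormals would mean that 50 of 60 people were judged not to have made full effort.

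Sensitivity is the first objective, and this sentence is its only precision justification. If a measure ends with well under 50 abnormals, its interval will be wider than the plan leads readers to expect.

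**Working it through.** **Inputs.** From Sample Size: 60 participants, 50 abnormal, sensitivity p from 0.77 to 0.96, two-sided 95% CI, stated widths 8.7% and 25.3%. The article does not name the interval method, so it was inferred by matching the stated figures. Per-measure abnormal counts n below 50 are assumptions, shown as a range.

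**Formula.** Continuity-corrected Wald half-width: h = 1.96 × √(p(1−p)/n) + 1/(2n). The limits are p − h and p + h, with the upper limit cut at 100% where it exceeds it.

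**Step 1: the 25.3% end (p = 0.77, n = 50).** h = 1.96 × √(0.77 × 0.23/50) + 0.01 = 0.1166 + 0.01 = 0.1266. Width = 2h = 25.3%, which matches. Plain Wald gives 23.3%, Wilson 22.8% and Clopper-Pearson 24.8%. The match supports both the method and a denominator of 50.

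**Step 2: the 8.7% end (p = 0.96, n = 50).** h = 1.96 × √(0.96 × 0.04/50) + 0.01 = 0.0543 + 0.01 = 0.0643. The upper limit exceeds 1 and is cut, so the width is 0.04 + 0.0643 = 10.4%, not 8.7%. Other methods at n = 50 give 9.4% (Wald, truncated), 10.9% (Wald), 12.4% (Wilson), 12.9% (continuity-corrected, not truncated) and 13.2% (Clopper-Pearson); none gives 8.7%. With p = 0.97: h = 0.0473 + 0.01 = 0.0573, width = 0.03 + 0.0573 = 8.7%. The stated figure therefore corresponds to 97%.

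**Step 3: the same method with fewer abnormals on a measure.** Total width:

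| Abnormal in person on the measure | Sensitivity 77% | Sensitivity 96% |
|---|---|---|
| 50 | 25.3% | 10.4% |
| 40 | 28.6% | 11.3% |
| 30 | 33.5% | 12.7% |
| 20 | 41.9% | 15.1% |
| 15 | 47.6% | 17.3% |

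For example, at n = 30 and p = 0.77: h = 1.96 × √(0.1771/30) + 1/60 = 0.1506 + 0.0167 = 0.1673, so 2h = 33.5%. By this method 50 is the smallest count that gives 25.3% at 77%.

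**Step 4: what 50 with any abnormality would imply.** If 50 people each have at least one abnormality among six measures, the average count per measure can lie anywhere from 50/6 = 8.3 (one abnormality each) to 50. All six measures reach 50 only if the same 50 people are abnormal on all six.

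**The case against.** The strongest reply is that the plan foresees low abnormality after concussion and acts on it. The remark that examinations are often normal introduces the decision to enrol more severe injuries, and purposive sampling is aimed at every domain. The abnormal-finding phrase can also be read as a working rate for each measure, and a range of assumed sensitivities fits planning across several measures. Some measures offer many ways to be abnormal: Table 1 has six balance conditions, six neck movements, and two VOMS criteria. If failing any one component counts, which is not stated, high rates are plausible there.

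Much of this stands. A reader might infer that far fewer than 50 will be abnormal on each measure and that the stated widths will not be delivered. The documents do not support that, because they give no per-measure rate. A reader might also compute 1 − (1 − 50/60)^(1/6) = 25.8%, about 15 people per measure. That requires the any-abnormality reading and six independent, equally frequent abnormalities; in a sample enriched with severe injury, deficits may well cluster, which would raise the counts. Nor is there ground to criticise an any-abnormal composite, since no section defines one.

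What the reply does not answer is that enrichment and purposive sampling aim at coverage of the domains. They fix no number per measure, so they do not secure 50 of 60 on each. The point is also not detail left to an analysis plan: the article states specific widths, and those widths depend on a count that it does not tie to the analysis it describes.

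**Conclusion.** The point holds in a limited form. The 25.3% applies to a measure with 50 in-person abnormals, and the plan neither states nor secures that number for any measure. With 15 to 40 abnormals, the width at 77% sensitivity would be 28.6% to 47.6%, and at 96% it would be 11.3% to 17.3%. These figures rest on the inferred interval method and on assumed counts. The 8.7% end is a separate arithmetic slip: with 50 abnormals it belongs to 97%, and 96% gives 10.4% by the same method.

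This should be fixed, but it does not undermine the study. Sensitivity carries no threshold, hypothesis or decision rule; the article calls the information preliminary (Projected Significance); and no estimate changes when the planned precision is restated.

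**What to change.** 1. State whether the 83% means any abnormality or an assumed rate for each measure.
2. Replace the single range of widths with precision per measure over plausible abnormal counts, as in the table above, and name the interval method.
3. Correct the 8.7% (and its 4.4% margin of error): either give 10.4% for 96%, or state 97% as the upper sensitivity if that was intended.
4. Count in-person abnormals per measure among the 39 participants assessed by May 2024, and direct the remaining purposive recruitment (60 − 39 = 21 at that date) toward the domains with fewest. If recruitment has since closed, report the achieved count beside each sensitivity estimate.

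The cost is stated precision that looks less favourable, and one REDCap query. No extra participants are needed.

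### The best-case precision for sensitivity (8.7% width, 4.4% margin) does not follow from 96% sensitivity in 50 abnormal participants; standard 95% intervals are about 11% to 14% wide

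*Protocol article*

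**What the plan says.** The Sample Size section gives every input for the sensitivity objective in one sentence. The total is 60 participants, "50 (83%) of whom are expected to have an abnormal finding, and an estimated sensitivity ranging from 77% to 96"%. From these it concludes that "the two-sided 95% CI around the estimated sensitivity will have a total width ranging from 8.7% to 25.3% (or margin of error 4.4%-12.7"%. No interval method is named. The Method-Comparison (Sensitivity) Analysis section defines sensitivity as true positives over true positives plus false negatives, with the in-person finding as reference. The denominator for this calculation is therefore the 50 participants expected to be abnormal in person.

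**The concern.** The two stated widths should come from one method applied at 77% and at 96% with 50 participants. A hand check of the upper value fails at once: the simplest interval for 96% with n = 50 is already about 11% wide, and methods that behave better near 100% give more.

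This sentence is the only precision given for the study's first objective and the only sample-size reasoning attached to it. The overstated end also affects interpretation. A reader who takes 96% with a 4.4-point margin at face value expects a lower limit of 96 − 4.4 = 91.6%. The exact lower limit is 86.3%. If the virtual assessment does well, the lower limit is what tells a clinician how many deficits it might still miss.

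**Working it through.** **Inputs** (Sample Size section): n = 50 abnormal participants; sensitivity p = 0.77 and 0.96; two-sided 95%, so z = 1.96. I take 96% as 48/50. Since 77% of 50 is 38.5, the exact value at 77% treats the count as continuous; it lies between the values for 38/50 (25.1%) and 39/50 (24.4%).

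**Step 1: reproduce the wide end.** Wald width with continuity correction is 2 × [z√(p(1−p)/n) + 1/(2n)].

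- p = 0.77: √(0.77 × 0.23/50) = 0.0595; 2 × (1.96 × 0.0595 + 0.01) = 0.2533, or **25.3%**. Half is 12.7%. Both match the article.
- Plain Wald at 0.77 gives 23.3%, which does not match.

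**Step 2: apply the same method at 96%.**

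- √(0.96 × 0.04/50) = 0.0277; 2 × (1.96 × 0.0277 + 0.01) = **12.9%**.
- The half-width is 0.0643, so the nominal upper limit is 102.4%. Cut at 100%, the width is 0.04 + 0.0643 = **10.4%**.

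Neither is 8.7%.

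**Step 3: try other methods at n = 50.**

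| Method | Width at 96% | Width at 77% | Distance from 96% to lower limit |
|---|---|---|---|
| Stated | 8.7% | 25.3% | margin given as 4.4 |
| Wald | 10.9% (9.4% if cut at 100%) | 23.3% | 5.4 points |
| Wald, continuity-corrected | 12.9% (10.4% if cut) | 25.3% | 6.4 points |
| Wilson | 12.4% | 22.8% | 9.5 points |
| Exact (Clopper-Pearson) | 13.2% (86.3% to 99.5%) | 24.8% | 9.7 points |

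The arcsine, t-based Wald, Jeffreys, logit, Agresti-Coull and continuity-corrected Wilson intervals give 10.7%, 11.1%, 11.4%, 13.6%, 13.9% and 14.2% at 96%. The full range without truncation is 10.7% to 14.2%. With truncation, the Wald types give 9.4% to 10.4%. None reaches 8.7%.

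**Step 4: look for the source.** With continuity-corrected Wald cut at 100% and p = 0.97, √(0.97 × 0.03/50) = 0.0241, the half-width is 1.96 × 0.0241 + 0.01 = 0.0573, and the width is 0.03 + 0.0573 = **8.7%**. One method thus gives both stated widths, but only if the upper sensitivity is 97%. This is an inference; the article does not say it.

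**Step 5: the margin.** 8.7/2 = 4.35, printed as 4.4%. If the interval was cut at 100%, it is not symmetric about the estimate and half its width is the distance to neither limit. By that same method the lower limit is 6.4 points below 96%, or 5.7 points below 97%.

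**Step 6: could a different denominator explain it?** With all 60 participants abnormal, Wald at 96% is 9.9% (9.0% if cut) and continuity-corrected Wald cut at 100% is 9.8%. A width of 8.7% at 96% needs about 78 abnormal participants (Wald), 92 (Wilson) or 103 (exact). With truncation it needs about 66 (Wald) or 86 (continuity-corrected). Every figure exceeds the whole sample.

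**The case against.** The best defence accepts that 8.7% is wrong and argues that little depends on it. The protocol sets no target width, no minimum lower limit and no success threshold for sensitivity, and it plans no claim from a lower confidence limit. Precision planning rests on the wide end, which is correct. The final interval will come from the data, so a planning figure cannot bias the result. The cause may be one mistyped input: on the apparent method the gap is 10.4% against 8.7%, or 1.7 points, which is smaller than 11% to 14% suggests. Setting 9.7 points against 4.4 also changes both the method and the quantity compared.

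Much of this stands as a limit on the consequences. The error sits only at the optimistic end, and the target of 60 does not depend on it. The 11% to 14% range is for full-width intervals, and the like-for-like distance to the lower limit is 6.4 points. But none of it makes the printed figure right. Even the most favourable reading, plain Wald cut at 100%, gives 9.4%, and that method contradicts the stated 25.3% at the other end. Nor is this a detail left to an analysis plan: the stated result does not follow from inputs in the same sentence.

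**Conclusion.** The concern holds. With 50 abnormal participants and 96% sensitivity, the two-sided 95% interval is about 11% to 14% wide by standard methods, or 9.4% to 10.4% if a Wald-type interval is cut at 100%. It is not 8.7%. The 4.4% margin is wrong too: the lower limit lies 5.4 points away by Wald, 6.4 by the method that reproduces the other end, and 9.7 by the exact method. The 25.3% and 12.7% figures at 77% are correct for continuity-corrected Wald.

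The conclusion assumes only the article's own inputs and one independent observation per abnormal participant. That 97% was used in place of 96% is likely but cannot be confirmed from the article. The only precision statement for the first objective needs correcting, although neither the sample size nor the planned analysis changes as a result.

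**What to change.** Check first whether the 96% or the 8.7%/4.4% was misentered. Then name one interval method suited to proportions near 100%, and give both ends by it. Suggested text:

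> With 50 participants abnormal on the in-person assessment, the exact (Clopper-Pearson) 95% confidence interval for sensitivity would be about 13.2 percentage points wide at an observed 96% (lower limit about 86%) and about 24.8 points wide at 77% (lower limit about 63%).

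The Wilson widths would be 12.4% and 22.8%. If the authors prefer to keep the method behind 25.3%, the matching value at 96% is 12.9%, or 10.4% with the truncation stated. In every case, drop the symmetric margin of error at the high end and quote the expected lower limit, and use the same method when the results are analysed.

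The cost is a text change. The stated precision becomes less favourable; the sample size, recruitment and data collection are unaffected.
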